#### Follow-Up of Study Participants

In order to better understand reasons for refusal and survey attrition, to assess the usability of the IVR platform, and to receive feedback on the incentives and survey introductions, we will call a sub-sample of participants from each sub-study and administer a short MPS. For each of these sub-studies, we will call back a random sample of 30 individuals who (1) were age-eligible and consented but did not complete the survey; (2) refused to consent to the survey; and (3) were identified as non-responders (ie, listened to a portion of the survey introduction but disconnected from the survey).

### Questionnaire

Experts in NCDs, mobile health, and survey methodology convened in 2015 to develop a NCD risk factor questionnaire that could be adapted to a MPS. Questions were selected from standardized surveys such as World Health Organization (WHO) STEPwise Surveillance and Tobacco Questions for Surveys [9,10]. Question selection was guided by the Global Monitoring Framework for NCDs, which included the main behavioral NCD risk factors (physical activity, alcohol consumption, tobacco use, and diet) [11]. Questions were selected independent of their perceived adaptability to an IVR platform.

**Figure 1 figure1:**
[figure not shown]
Study design for sub-study 7.

The questionnaire is comprised of the following parts: (1) language selection, (2) introduction, (3) age screening, (4) consent, (5) demographic questions, (6) NCD modules, and (7) airtime delivery, as applicable (Figure 2). NCD modules are groups of topically similar NCD risk factor questions (eg, tobacco, alcohol, diet, physical activity, etc). The order of the modules will be randomly assigned. For example, one participant may be presented with questions on diet first, followed by tobacco, then alcohol, and finishing with physical activity; another respondent may be presented alcohol questions first, and then diet, then physical activity, and finally tobacco. However, the questions within each module will not be randomized.

The questionnaire will be translated into local languages with input from members of local collaborators and communities to help ensure appropriate syntax and semantics and then back-translated to ensure accuracy. After the questionnaire’s translation has been deemed acceptable, country residents fluent in the survey languages will narrate and audio record the survey. The audio recording of the survey will be uploaded into VOTOmobile’s IVR platform. VOTOmobile is a Ghana-based organization that works to develop mobile phone survey systems.

**Figure 2 figure2:**
[figure not shown]
Sequence of the mobile phone survey.

### Survey Delivery and Data Collection

Unless otherwise indicated, the logistics and timing of MPS delivery will be similar for all sub-studies. When a randomly dialed number is connected (ie, a respondent picks up the phone), the respondent will be presented with a brief pre-recorded introduction to the study and provided an opportunity to select the survey’s language. For IVR sub-studies, respondents will select a language by entering their response on their mobile phone keypad (eg, “If you would like to listen in English, press 1”).

After the language selection, the speaker will provide a more detailed description of the study that includes the purpose, duration, risks, benefits, sponsoring agency, and requirements to receive an incentive. For sub-study 4, participants in the motivational introduction arm will receive added sentences and language expressions that may further motivate them to participate in the survey. After hearing the survey’s introduction, participants will be screened for eligibility based on their age; those who indicate being less than 18 years old will be thanked for their interest and the survey will be terminated. Participants will then be asked to press a number on their keypad to indicate their willingness to continue (eg, “Press 1 if you would like to participate in this survey, press 3 if you do not want to participate in the survey”). Respondents will be asked a series of demographic questions followed by NCD modules whose order of presentation is randomized as described above.

Surveys will only be sent to participants once. Participants who were ineligible due to age, refused consent, or opted out during the survey will not have an additional survey sent. The MPS will be delivered at random times ranging from 8:00 AM to 8:00 PM local time. The exact time window to deliver the MPS will be determined by each country during the formative phase.

### Proposed Sample Sizes

Assuming a baseline survey completion percentage of 30%, in order to detect an absolute 10% difference in survey completion between two study arms at an alpha of .05 and power of 80%, it is calculated that 376 individuals who have completed an IVR survey will be needed in each study arm for each sub-study. With a completion percentage of 30%, we calculated that 1254 participants would be required to consent to the survey per study arm in each country. With 16 study arms total in these 6 sub-studies, 20,064 participants will be enrolled in each country (Table 4). We have not inflated the sample size for multiple comparisons as per the recommendation by Rothman [12]. We chose a 10% difference between study arms as our preliminary analysis indicated that a 1 dollar incentive becomes cost-neutral at this cut-off point.

**Table 4 table4:** Number of participants needed to complete a mobile phone survey per country.

Sub-study	Study arms	Participants who completed survey per study arm, n	Total participants who completed the survey, n
Sub-study 1	3	376	1128
Sub-study 2	3	376	1128
Sub-study 3	3	376	1128
Sub-study 4	4	376	1504
Sub-study 5	2	376	752
Sub-study 6	1	376	376
Sub-study 7^a^	2	405	810
Total			6826

^a^For sub-study 7, we adjust for a 20% loss to follow-up from the first and second mobile phone survey.

For sub-study 7, the sample size is calculated based on the kappa statistic [13]. With assumption of kappa .75, a margin of error of 0.05%, an alpha of .05, and the proportion of positive responses of 0.3, 405 participants who have completed the survey per study arm are needed. Adjusting for a 20% loss to follow-up from the first and second mobile phone survey and a 30% baseline completion percentage, 1688 participants who consented will be enrolled per arm, for a total of 3376 participants across the two arms for each country.

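### The 376 per arm is the denominator of the completion proportion, not a count of completers, so dividing it by 0.30 to reach 1254 applies the completion rate twice and misstates the design's power

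*Protocol article*

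**What the plan says.** The Proposed Sample Sizes section of the protocol article starts from a 30% baseline completion percentage and sets its aim as follows: "in order to detect an absolute 10% difference in survey completion between two study arms", with alpha .05 and 80% power. Its conclusion is: "it is calculated that 376 individuals who have completed an IVR survey will be needed in each study arm for each sub-study". The next step is: "With a completion percentage of 30%, we calculated that 1254 participants would be required to consent to the survey per study arm in each country". Multiplying by the 16 arms of sub-studies 1 to 6 gives 20,064.

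Table 4 also presents 376 as the number of completed surveys per arm. The section says that no inflation was made for multiple comparisons. It justifies the 10-point target on the ground that "our preliminary analysis indicated that a 1 dollar incentive becomes cost-neutral at this cut-off point".

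Data Management and Analysis lists the completion proportion among the main outcomes and defines a complete interview as five or more modules answered by an age-eligible respondent.

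**The concern.** Completion is the event being compared. A two-proportion formula returns the number of people per arm in whom that event either happens or does not. Among completers alone, completion is 100% in every arm and there is nothing to compare. Dividing by 0.30 treats completion as if it were dropout before the outcome is observed, although the 30% has already entered the formula as the baseline proportion.

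Two things are at stake. The stated power and detectable difference do not describe the design that would be enrolled. The enrolment presented as necessary is also well above what the stated target needs, which means more calls to the public and, in the incentive arms, more airtime.

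**Working it through.** **Inputs** (Proposed Sample Sizes): p1 = 0.30, absolute difference d = 0.10, alpha = .05, power = 80%. The section does not state sidedness or direction. Two-sided with p2 = 0.40 reproduces its figure, and equal arms are assumed. The mean proportion is 0.35, and z = 1.960 and 0.8416.

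**Step 1: reproduce 376.**
- Uncorrected: n = [1.960 × √(2 × 0.35 × 0.65) + 0.8416 × √(0.30 × 0.70 + 0.40 × 0.60)]² / 0.10² = (1.3221 + 0.5646)² / 0.01 = 355.9, so 356.
- With continuity correction: n′ = (n/4) × [1 + √(1 + 4/(n × d))]² = (355.9/4) × [1 + √(1 + 4/35.59)]² = 375.7, so **376**, an exact match.
- Variants that do not match: one-sided 281 (300 corrected); 30% versus 20%, 294 (313 corrected).

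So 376 is the denominator of each arm's completion proportion. It would contain about 113 completers at 30% (376 × 0.30) and about 150 at 40% (376 × 0.40).

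**Step 2: reproduce the inflation.** 376 / 0.30 = 1253.3, so 1254; and 1254 × 16 = 20,064. Both match.

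**Step 3: power of the design as enrolled.** Power = Φ{[d − 1.960 × √(0.455/n)] / √(0.45/n)}, where 0.455 = 2 × 0.35 × 0.65 and 0.45 = 0.21 + 0.24.
- n = 376: (0.1 − 0.0682) / 0.0346 = 0.920, so 82.1%. With continuity correction, d is replaced by d − 1/n and power is 80.0%.
- n = 1254: (0.1 − 0.0373) / 0.0189 = 3.31, so about **99.95%**, with or without the correction.
- If each arm instead recruits until it has 376 completers, the arms have 376/0.30 = 1253 and 376/0.40 = 940 consenters, and power is about 99.8%.

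**Step 4: detectable difference at 1254 per arm.** Solving for p2 above 0.30 gives about **5.2 points** at 80% power and about 6.1 points at 90%.

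**Step 5: enrolment ratio.** 1254 / 376 = 3.3. If arms recruit to 376 completers, an arm at 40% completion has 940 / 376 = 2.5 times the number needed.

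**Step 6: could multiplicity explain 1254?** The section says it was not allowed for. Even at alpha/3 or alpha/6, the corrected sample size is 495 or 570 per arm, and power at 1254 stays above 99%.

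**Sub-study 7.** Agreement between modes can be assessed only in people who completed the surveys, so dividing by the completion rate is legitimate there: 405 / 0.8 / 0.3 = 1687.5, so 1688, as stated.

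**The case against.** **The error is on the safe side.** This stands. More participants than needed leave nothing underpowered, bias no estimate and do not raise type I error. It does not make the stated power correct.

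**The completion denominator is in Figure 3, which is not shown.** Age screening comes before consent, so the denominator may include age-eligible people who refuse. This limits how exactly the power at 1254 can be stated. It does not rescue the label, because no completion proportion has completers alone as its denominator. The plan's use of 30% to convert completers to consenters also points to consenting participants.

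**376 completers may be wanted for something else.** Study Design makes demographic representativeness an outcome of every sub-study, and results are to be tabulated by question number and content. The article does not give this as the reason for 376, but it is a fair caution against simply cutting enrolment to 376, which would leave about 113 completers in an arm at 30%.

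**Stronger readings that the article does not support.**
- At 1254 per arm an observed gap of about 3.6 points would be significant (1.960 × √(2 × 0.3 × 0.7 / 1254) = 0.036). A reader might infer that incentives that do not pay for themselves would be adopted. Nothing in the article adopts an incentive on p < .05. The one selection rule, in Sub-Study 7, takes the incentive with the highest response and completion rates.
- A reader might want 10 points as a general threshold for calling an incentive worthwhile. The cut-off is tied to a 1 dollar incentive only. X is still to be set, other arms pay 2X or a lottery of at least 5X, and the arms of sub-studies 4 and 5 share one incentive.
- A reader might multiply the excess of 878 per arm (1254 − 376) over the 31 arm-by-country cells in Table 3 (16 + 13 + 2) and report about 27,200 surplus participants. That assumes every arm enrols 1254, and it uses Table 3's country allocation where the sample-size text gives 20,064 for each country. It is not an exact figure.

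**Conclusion.** The point holds as a misstatement of sample size and power. The 376 is the number per arm in whom completion is observed. Calling it completers, in the text and in Table 4, and dividing by 0.30 applies the completion rate twice. The design described has about 99.95% power for 10 points (about 99.8% if arms recruit to 376 completers), not 80%, and 80% power for about 5.2 points. The enrolment needed for the stated target is overstated by up to 3.3 times.

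These figures assume a two-sided test, equal arms, 30% versus 40%, and a denominator of consenting, age-eligible participants. Sub-study 6 has one arm, so the calculation applies there only through a comparison with an arm from another sub-study. The validity of the comparisons is not in question.

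**What to change.** Choose one of the following and edit the Proposed Sample Sizes section to match.

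1. **Keep 1254 per arm and restate its properties:** over 99% power for 30% versus 40%, and 80% power for a difference of about 5 points from 30%. In Table 4, present 376 as the completers expected at 30% (1254 × 0.30 = 376.2), not as the number that the power calculation requires. This costs a few sentences and leaves the design untouched.
2. **Size for the stated target only:** relabel 376 as participants in the completion denominator, replace 1254 with 376 and 20,064 with 376 × 16 = 6,016, and correct Table 4. First check that 376 per arm suffices for response, refusal, representativeness and the stratified tabulations. This lowers cost.

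If 376 completers per arm are wanted for another purpose, give that reason separately from the power statement. Under either option, name the completion denominator and the sidedness of the test beside the calculation. Sub-study 7 needs no change on this point.

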#### Sub-Study 7: Survey Modality

This sub-study evaluates the effect of the survey modality (IVR versus CATI) on the survey’s response and completion rates and assesses the inter-modal reliability. Participants will be randomized to 1 of 2 arms: (1) IVR then CATI; or (2) CATI then IVR. Participants in the first study arm will receive an IVR survey first, followed by a CATI survey 7 days later (Figure 1). Participants in the second study arm will receive a CATI survey first followed by an IVR survey 7 days later. At initial enrollment, it will be clearly explained to participants that they are being enrolled in a study where they will be contacted twice. The questionnaires used in both study arms will be the same. This crossover design will allow for an assessment of response consistency, adjusted for the risk of “priming” after exposure to the prior modality. This is the only sub-study that will require participants to answer the NCD survey twice. The amount, timing, and structure of incentive will be guided by the first 3 sub-studies where the incentive that yielded the highest response and completion rates will be provided to all participants in sub-study 7. This sub-study will be conducted in Bangladesh and Tanzania.

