### Data Management and Analysis

The main outcomes in this study are contact, response, refusal, and completion proportions. Our outcomes are defined based on standard definitions from the 9th edition of the American Association for Public Opinion Research (AAPOR) [14], with some modifications to accommodate our RDD MPS design. Eligible individuals will be defined as persons who confirm that they are at least 18 years old.

Complete interviews (CI) are defined as age-eligible respondents who answer 5 or more modules. Partial interviews (PI) are defined as age-eligible respondents who answer between 2 and 4 modules. Participants who are age-eligible but answer less than 2 modules will be classified as a refusal/break-off (R). Non-contacts (NC) are defined as a confirmed number where respondent never picks up (this classification only applies to sub-studies 6 and 7). The main outcomes will be calculated using the equations in Figure 3.

Outcomes will be tabulated and stratified by both the question number and the question content due to the randomization of NCD topic modules. As a secondary analysis, we will conduct Kaplan-Meier curves to plot survey attrition by time spent on survey. For sub-study 7, test for agreement in survey responses between the survey modalities will be assessed using Cohen kappa. Statistical significance will be determined at an alpha of .05.

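### Sub-study 7's kappa margin is misstated: the stated inputs give ±0.05 on the kappa scale for 810 pairs in total, not 0.05% for 405 per arm

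*Protocol article*

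**What the plan says.** Under Proposed Sample Sizes, sub-study 7 is sized on the kappa statistic. The inputs are: "With assumption of kappa .75, a margin of error of 0.05%, an alpha of .05, and the proportion of positive responses of 0.3". The stated result is that "405 participants who have completed the survey per study arm are needed". Table 4 lists two arms of 405 and a total of 810 per country. Allowing for 20% loss between the two surveys and 30% completion, the text arrives at 1688 consenting participants per arm and 3376 per country.

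The section on sub-study 7 defines the two arms as the two orders, IVR then CATI and CATI then IVR. It gives a reason for the layout: "This crossover design will allow for an assessment of response consistency", with an adjustment for priming by the modality met first. Under Data Management and Analysis, "test for agreement in survey responses between the survey modalities will be assessed using Cohen kappa". That sentence does not say whether the kappa is pooled over the orders, stratified by order, or reported by order.

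**The concern.** Two features of the precision statement do not fit together. First, kappa is not a percentage, and a half-width of 0.05% (0.0005) is out of reach for any survey of this size. Second, the margin is tied to a number per arm, although a kappa over the whole sub-study would use the pairs from both arms. Because the arms are the orders, the sentence reads as a promise of the stated margin within each order.

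This is the only sample-size basis given for inter-modal reliability, which is a named objective and an outcome specific to sub-study 7. A reader who relies on it would expect order-specific agreement to be more precise than it will be. Anyone who reuses 405 per arm as the requirement for ±0.05 in a single sample would recruit half of what is needed.

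**Working it through.** **Inputs, all from Proposed Sample Sizes:** kappa k = 0.75; positive proportion p = 0.3; alpha = 0.05; 405 completers per arm, 810 in total; 20% loss; 30% completion. Assumption: the article does not state sidedness, so a two-sided 95% interval is used.

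**Variance.** For two ratings of a binary item with the same prevalence in both, the large-sample variance of kappa is V/n, with

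V = (1−k)[(1−k)(1−2k) + k(2−k)/(2p(1−p))]
= 0.25 × [0.25 × (−0.5) + 0.75 × 1.25/0.42]
= 0.25 × (−0.125 + 2.2321) = 0.5268.

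The general large-sample kappa variance with equal marginals gives the same value. The simpler Cohen variance gives 0.5327.

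**Reproducing the plan's figure.** For a half-width m, n = (1.96/m)² × V.

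- m = 0.05: n = 1536.64 × 0.5268 = 809.5, rounded up to 810. This equals 2 × 405 and the Table 4 total.
- m = 0.0005 (0.05% taken literally): n is about 8.09 million.

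No variant tried turns m = 0.05 into 405. One-sided alpha gives 570, and the simple Cohen variance gives 819. Changing the margin does not produce 405 either: m = 0.07 gives 413 and m = 0.10 gives 202. So 405 is the 810 total divided by two.

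**Precision the design delivers, in each country.**

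| Estimate | Calculation | Half-width |
|---|---|---|
| Kappa over both orders, 810 pairs | 1.96 × √(0.5268/810) | 0.050 |
| Kappa in one order, 405 pairs | 1.96 × √(0.5268/405) | 0.071 |
| Difference between the two orders | 1.96 × √(2 × 0.5268/405) | 0.100 |

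The equally weighted mean of the two order-specific kappas has variance (1/4) × 2 × V/405 = V/810. A stratified estimate therefore also has a half-width of about 0.050, if kappa and prevalence are the same in both orders.

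**Enrolment.** 405/0.8/0.3 = 1687.5, so 1688 per arm; 2 × 1688 = 3376. Both figures reproduce. They also show that 405 is the number of pairs before inflation for loss, although the Table 4 footnote could be read as if the loss were already included in it.

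**Dependence on prevalence.** With k held at 0.75, the half-widths for 810 and 405 pairs are 0.078 and 0.110 at p = 0.1, and 0.046 and 0.064 at p = 0.5. The ±0.05 belongs to p = 0.3.

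**The case against.** The strongest defence is that the design is sized correctly and only the sentence is loose. The percent sign is most likely a typographical slip, since the sample size and the enrolment figures all follow from 0.05 absolute and nothing later uses 0.0005. Read as an allocation, 405 in each of two arms is exactly what a total of 810 requires. All of this stands, and it is why no further participants are needed. It does not rescue the sentence, which gives a wrong unit and attaches the margin to one arm without saying that it belongs to both together.

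Three stronger readings are tempting, and the documents do not support them.

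- A reader might infer that the design misses a promised ±0.05 within each order. Apart from the ambiguous per-arm wording, the article claims no precision for order-specific kappas or for their difference.
- A reader might infer that the planned kappa ignores order and so cannot handle priming. The analysis section does not say that it is unstratified, the design section states the intention to adjust, and how this is done is a detail that an article commonly leaves to the full protocol or analysis plan.
- A reader might apply the 30% completion figure to the second survey and expect far fewer pairs. That figure is completion among people who consent at a first contact. The 20% loss concerns people who have already completed one survey and were told at enrolment that they would be contacted twice. Nothing in the article supports 30% for the second survey.

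**Conclusion.** The precision statement for sub-study 7 is wrong as written. The margin should be 0.05 on the kappa scale, 100 times the printed value, and it belongs to 810 pairs over both orders. At 405 pairs the half-width is about 0.071, which is √2 times the intended margin. The planned total meets ±0.05 for a pooled or order-stratified kappa, so this is an error in a stated figure and not a shortfall in the design. Inter-modal reliability comes in addition to the main outcomes of contact, response, refusal and completion, and none of those is affected. The result rests on the article's own kappa and positive proportion, a two-sided 95% interval, the large-sample variance, and 405 usable pairs per arm.

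**What to change.** In Proposed Sample Sizes, replace the 0.05% by a two-sided 95% margin of ±0.05 in absolute kappa units, and say that it applies to the 810 pairs combined over both orders in each country. Add that each order alone gives about ±0.071 and that the difference between orders has a margin of about ±0.10. Keep 405 per arm as the allocation, and 1688 and 3376 as the enrolment. In the Table 4 footnote, make clear that 405 is the number before inflation for the 20% loss.

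Optional, because the design section speaks of adjusting for priming: say that the kappa will be stratified by order and reported beside the two order-specific kappas. The stratified estimate keeps about ±0.05.

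The cost is a few words, and one simple stratified analysis if the option is taken. No further participants are needed.
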